**Fig. 3 Fig3:**
[figure not shown]
Power estimates and detectable alternatives by sample size in the SEPVADIS trial

#### Data analysis plan

The intent-to-treat analysis will include all randomized subjects. Hypothesis testing will use two-sided α = 0.05 without correction for multiplicity. We will characterize subjects regarding baseline and follow-up 6MWD and other endpoints. We will summarize demographics and other predictors of clinical status. Continuous variables will be summarized by the mean, median, standard deviation, and range, as appropriate. The distribution of the outcome measures of interest will be assessed for normality. If the distribution is normal, we will use independent t-tests to compare by treatment assignment. If the distribution is not normal, we will transform the data to meet the assumption of normality. If transformation does not achieve normality, comparisons between groups will be made using the Wilcoxon rank-sum test. We will use contingency tables for discrete and dichotomous variables.

The primary analysis will compare the absolute change in 6MWD from baseline with adjustment for baseline 6MWD, age, and sex in linear regression models. We chose sex as a potential confounder of the relationship between 6WMD and treatment based upon prior work demonstrating there may be worse survival for men with SSc-PAH compared to women [37], but men may have improved 6MWD and HRQoL compared to women in response to PDE-5 inhibitors [38]. Given the small sample size of our study, we will be sensitive to overfitting our model with covariates but will use the univariate analyses to inform the inclusion of additional covariates in the final model. We will examine the clinical relevance of the change in 6MWD by comparing the proportion of patients who achieve the MID for the 6MWD for both PAH (MID = 33 m) and for SSc-PAH (MID = 24 m) by treatment assignment. Using separate multivariable logistic regression models adjusting for baseline walk distance, age, and sex, we will assess if the odds of achieving a clinically relevant improvement in 6MWD based upon the MID for PAH and for SSc-PAH differs by treatment assignment. We can then perform responder analyses to determine characteristics of SSc-MEP patients likely to achieve either MID for the primary outcome of 6MWD.

The secondary outcomes will be analyzed similarly using linear regression models adjusting for baseline values and for sex. Prior studies have demonstrated sex-specific differences in RV structure and function as assessed by CMR [39] and in PAC [29], though to our knowledge there are no studies examining differences in TAPSE between men and women. HRQoL measures may differ by sex as well.

We will also include longitudinal models of change from baseline over the time of the trial. Exploratory multivariate analyses will be performed incorporating all the available endpoint assessments (baseline, 4 months, and 12 months) in an ANCOVA model with active treatment/placebo status as the independent variable.

We will attempt to minimize missing data by encouraging full subject participation and follow-up even if the subject stops the study drug prematurely. If there are missing data, we will perform sensitivity analyses using the mean value obtained to replace this missing data. For subjects lost to follow-up, we will use all the information available until the end of follow-up. For dropouts, we will use the lowest value obtained to replace missing data in separate sensitivity analyses.

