**Methods:**

The SEPVADIS trial is a randomized, double-blind, placebo-controlled phase 2 trial of sildenafil in SSc-MEP patients with a target enrollment of 30 patients from two academic sites in the United States. The primary outcome is change in six-minute walk distance after 16 weeks of treatment. Secondary endpoints include change in pulmonary arterial compliance by RHC and right ventricular function by cardiac magnetic resonance imaging at 16 weeks. Echocardiography, serum N-terminal probrain natriuretic peptide, and health-related quality of life is being measured at 16 and 52 weeks.

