Sildenafil is being purchased from Teva Pharmaceuticals, who are not involved in the planning or conduct of this trial. Participants are randomized to either sildenafil (20 mg) or matching placebo taken three times per day. Sildenafil and placebo tablets are being over-encapsulated by the Research Pharmacy at the Johns Hopkins University (JHU) School of Medicine Research Pharmacy. At the Research Pharmacy, capsules are being packaged into bottles with a liner, cotton, and childproof cap. One bottle of drug product is dispensed to study subjects at the baseline study visit and at the 16-week visit during the treatment phase. Subjects are asked to return bottles at the 16-week and 52-week visits to allow for tracking of adherence and medication control. Randomization to drug or placebo is done in a 1:1 fashion blocked and stratified by center. All study personnel, subjects, and the statistician are blinded for the duration of the study until the last subject completes follow-up assessments. The JHU Research Pharmacist is unblinded. In the rare event that unmasking is necessary for clinical care, the Chair of the Steering Committee will make the decision to unmask, and the treating physician will call the research pharmacy to obtain the participant’s treatment assignment. Subjects will be withdrawn from the trial if the participant withdraws consent or if the principal investigator determines that the subject should be withdrawn for safety. One specific scenario in which this could occur is if the participant has a mPAP > 25mmHg and a PAWP ≤ 15mmHg on their week 16 RHC; they would be withdrawn from the trial and given guideline-based PAH treatment.

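### Randomisation is stratified by center, but center is not a pre-specified covariate in the primary or secondary models; this costs power only if center predicts the adjusted change in 6MWD

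*Protocol article*

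**What the plan says.** The Interventions section states: "Randomization to drug or placebo is done in a 1:1 fashion blocked and stratified by center". There are two strata, because the abstract gives "a target enrollment of 30 patients from two academic sites in the United States".

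Under Data analysis plan, change in 6MWD is compared between arms "with adjustment for baseline 6MWD, age, and sex in linear regression models". The responder analyses use "separate multivariable logistic regression models adjusting for baseline walk distance, age, and sex". For the other endpoints the text reads: "The secondary outcomes will be analyzed similarly using linear regression models adjusting for baseline values and for sex". The longitudinal and exploratory ANCOVA models name treatment status and no center term.

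The same section warns about overfitting, yet says the investigators "will use the univariate analyses to inform the inclusion of additional covariates in the final model". Center is therefore not ruled out, but it is not named, and no reason is given for leaving it out. Testing is two-sided at 0.05.

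**The concern.** Stratified, blocked allocation makes treatment nearly orthogonal to center. The true sampling variance of the treatment estimate then contains almost no between-center component. A model without center still counts that component as residual noise. Where center matters for the outcome, the reported standard error exceeds the real one, the interval is wider than it need be, the type I error falls below 5%, and the precision gained from stratifying is not used.

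This is not a detail that the article leaves to a fuller document. It lists the covariates of both sets of models and justifies sex at some length, but the list omits the one factor that the design stratified on. Screening on univariate results is a poor substitute: center would enter only after outcome data are seen, and a test of center in about 27 patients will often miss a real effect.

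**Working it through.** **The plan's own figure.** Sample size gives more than 80% power for 45 m, SD 75 m and 27 subjects. For two arms of 13.5, SE = 75 × √(2/13.5) = 28.9 m and 45/28.9 = 1.56. Normal-approximation power is Φ(1.56 − 1.96) = Φ(−0.40), about 34%, so the stated figure is not reproduced as a two-arm comparison. That is a separate issue. It matters here only because the trial has little power to spare.

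**Inputs.** From the document: effect 45 m, SD 75 m, 27 completers, two centers, two-sided 0.05, covariates baseline 6MWD, age and sex. Assumed: completers split 15/12 between centers, blocks of 4, baseline to week-16 correlation 0.7, and the size of the center effect.

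**Approximate formula.** The residual SD after baseline adjustment is 75 × √(1 − 0.7²) = 53.6 m, so the variance is 5,625 × 0.51 = 2,869 m². A center-specific change of d metres, left out of the model, adds p(1 − p)d², where p(1 − p) = (15/27)(12/27) = 0.247. The standard error is inflated by √(1 + 0.247d²/2,869):
- 13 m: √(1 + 42/2,869) = 1.01
- 27 m: √(1 + 180/2,869) = 1.03
- 38 m: √(1 + 357/2,869) = 1.06
- 60 m: √(1 + 889/2,869) = 1.14
- 75 m: √(1 + 1,389/2,869) = 1.22

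**Simulation, center shifts the week-16 walk only** (6,000 trials per row, true effect 45 m):

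| Center-specific change | Power without center | Power with center | Type I error without center |
|---|---|---|---|
| 0 m | 49.8% | 48.9% | 4.8% |
| 13 m | 49.6% | 49.3% | 5.1% |
| 27 m | 47.6% | 49.8% | 4.4% |
| 38 m | 44.3% | 49.0% | 4.1% |
| 60 m | 38.3% | 49.6% | 2.9% |
| 75 m | 33.5% | 49.7% | 2.5% |

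At 38 m the mean 95% interval is 96.0 m wide without center and 91.1 m with it (96.0/91.1 = 1.05), in line with the formula. At 60 m it is about 14% wider.

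**Simulation, same shift at baseline and week 16.** Power without and with center was 48% and 49% (38 m), 48% and 50% (60 m), and 47% and 49% (75 m). Type I error without center was 5.0%, 4.9% and 4.8%. Interval width at 75 m was 91.7 m against 91.0 m. The reason is that a persistent shift cancels in the change score. Conditioning on baseline then leaves at most (1 − 0.7)d, for example 0.3 × 75 = 22.5 m, and the fitted baseline slope absorbs part of that.

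**Other splits and SDs.** With 30 enrolled as 15:15, 20:10 or 24:6, three dropouts, and a residual SD of 75 m or 40 m, omitting center changed nothing material for a center effect of 0 to 0.25 residual SD. It cost about 0–2 points of power at 0.5 residual SD and about 4–8 points at 1.0. On this scale the 38 m above is 38/53.6 = 0.71 residual SD and 75 m is 75/53.6 = 1.40.

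**The case against.** The strongest reply is that the usual sources of a center difference (walking course, coaching, case mix) act on both visits alike. The primary analysis takes change and adjusts for baseline, so it already removes most of such a difference, and the second simulation bears this out. The Outcomes section also says that testing was standardised between sites and that catheterisation, echocardiography and cardiac magnetic resonance studies from the second site are interpreted at the first, which weakens any argument from local equipment. The error, if there is one, is conservative: no bias and no excess false positives. All of this stands. Central reading is not stated for the walk test, the primary outcome, but that alone does not show a center effect on change.

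A reader might infer that the intervals are necessarily too wide and the test necessarily below nominal size. The document does not support that. It reports no center effect and no expected split, and with no center effect the two analyses perform alike. A reader might also infer that double-digit power losses are to be expected. Those need centers to differ by 60–75 m in change after baseline adjustment, and nothing in the document suggests this.

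The overfitting caution does not justify leaving center out. It argues against covariates chosen by screening, not against a single term fixed by the design.

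**Conclusion.** The mismatch between design and analysis is real, and its consequence is conditional. If center predicts the change in 6MWD after adjustment for baseline, age and sex, the stated primary model is conservative and loses power. On the assumptions above, the loss is about nil for a difference shared by both visits, about 2 points at 27 m, 4–5 points at 38 m, and 11–16 points only at an extreme 60–75 m. Against this, including an irrelevant center term costs at most about 1 point (49.8% against 48.9%). The trade favours inclusion, but this is an inexpensive improvement and not a threat to validity. The power figures were computed for the primary endpoint only. For the secondary models the same reasoning applies, but the size is unknown.

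**What to change.** Before unblinding, pre-specify center as a fixed effect in the primary linear model, which becomes treatment, baseline 6MWD, age, sex and center. Add it likewise to the secondary and longitudinal linear models. If the investigators prefer to omit it, they should say so in advance and give the reason. Its inclusion should not depend on the univariate screening. The cost is one line of wording and one degree of freedom per model, with no change to enrolment, visits or data collection.

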### Outcomes

The primary outcome of this trial is 6MWD measured at 16 weeks. Six-minute walk distance reflects peak oxygen consumption [22] in PAH and is associated with changes in HRQoL [23], with a minimal important difference (MID) of 33 m for PAH and 24 m for SSc-PAH [23]. The 16-week timepoint was chosen since nearly every proprietary drug for PAH has been approved based on changes in 6MWD at 3–4 months as this is considered a clinically important intermediate endpoint [17, 24–27]. Second, improvement in 6MWD in SSc-PAH patients can be seen in as few as 8 weeks in treatment-naïve patients [28]. We are following patients for one year and collecting 6MWD along with other data to assess the durability of the effect of sildenafil in SSc-MEP.

Secondary endpoints include change in pulmonary arterial compliance (PAC) and RV function by cardiac magnetic resonance imaging (CMR) and echocardiography, serum N-terminal probrain natriuretic peptide (NT-proBNP), and HRQoL at 16 weeks. Six-minute walk distance, NT-proBNP, HRQoL, and echocardiography are also obtained at 52 weeks. PAC is a measure of pulmonary arterial stiffness and a contributor to RV afterload which, due to the inverse hyperbolic relationship of PVR and PAC [29], may be modifiable early in the course of PAH. This is of significant relevance in SSc-PAH, since PAC is an independent predictor of survival [30]. Echocardiographic measures of RV function include tricuspid annular planar systolic excursion (TAPSE) [31] and speckle tracking echocardiography (STE), a quantitative measurement of regional and global contractility that is responsive to PAH treatment and correlates strongly with functional capacity and hemodynamics [32]. CMR, the gold standard for RV function assessment, is being employed to quantify RV ejection fraction and RV volumes. HRQoL is assessed using the Medical Outcomes Survey Short Form-36 (SF-36) [33] and emPHasis-10, a disease-specific tool developed specifically for PAH [34]. Testing protocols were standardized between the two enrolling sites; RHC, echocardiography, and CMR done at LSU will be interpreted centrally at Johns Hopkins.

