### Statistical methods

#### Sample size

We have based our effect size estimate of 45 m upon our preliminary data (not shown) demonstrating a difference in mean 6MWD between SSc patients with normal mPAP and SSc-MEP of ∼ 50 m with a standard deviation of 75 m. As such, we will have > 80% power to detect this difference at significance level of 0.05 with 27 subjects. To account for a 10% drop-out rate, we are enrolling 30 subjects. Even if our actual drop-out rate nearly doubles our expected rate (17% vs. 10%), we maintain adequate power to detect a difference of 45 m with 80% power (Fig. 3). While this estimate of change in 6MWD exceeds the MID for the 6MWD in PAH, the MID for this test in SSc-MEP is unknown. Further, if differences in 6MWD observed in the study do not reach the predefined detectable alternative, clinical relevance of the effect on 6MWD may be reflected by comparing the proportion of patients who exceeded the MID for 6MWD between arms. Based upon a sample size of 27 subjects completing the trial, we also have adequate power (80% or greater) to detect differences in the proposed secondary outcome measures. For instance, we have 80% power to detect a mean difference in PAC of 0.6 mL/mmHg (SD 1.1) between treatment arms; this difference was the average difference between these SSc-MEP and SSc-normal pressures found in our preliminary studies (data not shown). Further, we will have sufficient power to detect differences of 0.23 cm (SD 0.5) in TAPSE between groups which is close to the estimated MID for TAPSE in SSc-PAH (0.22 cm) from prior work from our group [28]. For global RV strain measured by STE, we have more than 85% power to detect a difference of 4.8% (SD 8%); this is the difference detected in our ATPAHSS Study of ambrisentan and tadalafil in treatment naïve SSc-PAH patients after therapy [28, 32]. Similarly, we have adequate power to detect a difference of 5% (SD 9%) in RVEF between arms; this difference is the MID for RVEF in PAH [35]. For HRQoL outcomes, we also have adequate power to detect clinically relevant changes in SF-36 of 5 units (SD 7 units) and emPHasis-10 of 6 units (SD 10) [36].

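### The primary regression is named, but its final covariates are left to univariate results from the trial's own data, and an unranked normality-gated test of the same outcome stands beside it

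*Protocol article*

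**What the plan says.** All of the relevant analysis text is in the Data analysis plan section of the protocol article.

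- **Error rate.** "Hypothesis testing will use two-sided α = 0.05 without correction for multiplicity".
- **Gated comparison.** The outcome measures of interest are checked for normality; 6MWD is not exempted. "If the distribution is normal, we will use independent t-tests to compare by treatment assignment". If not normal, the data are transformed, with no transformation named. "If transformation does not achieve normality, comparisons between groups will be made using the Wilcoxon rank-sum test".
- **Primary analysis.** The next paragraph names it: absolute change in 6MWD in a linear regression adjusted for baseline 6MWD, age and sex.
- **Extra covariates.** The same paragraph acknowledges the risk of overfitting in a small trial, but says the team "will use the univariate analyses to inform the inclusion of additional covariates in the final model".

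The Interventions section adds that randomization is blocked and stratified by center, and that the statistician stays blinded until the last subject has completed follow-up. The article does not say that the final model is settled before the blind is broken.

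**The concern.** A primary analysis protects the error rate only if it is determined before the treatment comparison can be seen. Here the core of the model is fixed and the rest is not. The covariate sentence is a positive commitment to let the trial's own data shape the final model. The only stated limit is an intention to be careful about overfitting.

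The gated comparison adds a second p-value for treatment against 6MWD. It follows directly on the statement of the two-sided significance level, so it reads as inference and not only as description. Nothing says which result decides if the two disagree.

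At stake is the meaning of a p-value just under 0.05 in a trial of 30 patients whose results are intended to inform a phase 3 study. A second cost is power: covariates chosen because they correlate with the outcome by chance use up degrees of freedom and can absorb part of the treatment effect.

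**Working it through.** **1. The plan's own figure.** The Sample size section says "we will have > 80% power to detect this difference at significance level of 0.05 with 27 subjects", for 45 m "with a standard deviation of 75 m". For two arms of 13.5 on average, power = Φ(Δ/(σ√(2/n)) − 1.96). Here 45/75 = 0.60, √(2/13.5) = 0.385, 0.60/0.385 = 1.56, and Φ(1.56 − 1.96) = Φ(−0.40) = 34%. With the t distribution and 13 versus 14 it is 32%. The stated figure does not reproduce for an unadjusted two-arm comparison. That is a separate matter and nothing below depends on it; 45 m and 75 m serve only as the effect and SD in step 4.

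**2. Type I error.** *From the documents:* 27 completers, 1:1 allocation (14 versus 13), two-sided 0.05, and the model with baseline, age and sex. *Assumed:* 5 or 10 candidate covariates, entry at univariate p < 0.10 or < 0.20 against change, and at most 4 added. The gate was taken as Shapiro-Wilk at 0.05, then t-test, then t-test on the shifted log, then Wilcoxon, all on change. There was no treatment effect, with 5,000 runs per row. The Monte Carlo standard error is √(0.05 × 0.95/5000) = 0.3 points at 5%, and 0.4 at 10%.

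| Candidates, entry p, outcome | Fixed | Screened | Gated | Fixed or screened | Fixed or gated | Any of three |
|---|---|---|---|---|---|---|
| 5, 0.10, normal | 5.3% | 4.8% | 5.3% | 6.0% | 7.2% | 7.8% |
| 10, 0.10, normal | 5.0% | 5.2% | 5.1% | 6.4% | 6.9% | 8.1% |
| 10, 0.20, normal | 5.1% | 4.8% | 4.8% | 6.7% | 6.9% | 8.3% |
| 10, 0.20, skewed* | 5.0% | 5.4% | 5.0% | 8.3% | 7.2% | 10.4% |
| 10, 0.20, heavy-tailed* | 5.2% | 5.0% | 4.8% | 7.5% | 6.7% | 9.0% |

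*Two of the ten candidates truly related to the outcome.

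The first three result columns are each rule used alone. The last three count a trial as positive if any listed test is significant. A separate simulation with 10 noise candidates gave 5.8% to 6.7%, 6.8% to 8.2% and 7.8% to 9.5% for those three columns. The fixed model and the gated test disagreed on significance in 3.5% to 4.5% of null trials.

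**3. Change or week-16 value.** If change is Y − B, the model Y − B = α + τT + βB + … is the same as Y = α + τT + (β + 1)B + …. The treatment effect τ, its standard error and its p-value are identical. In simulation they agreed in every trial.

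**4. Power for 45 m at SD 75.** The correlation r between baseline and week-16 6MWD is not in the documents, so it was varied. With 10 noise candidates screened at p < 0.10:

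| r | Fixed model | Screened model | Gated test on change |
|---|---|---|---|
| 0.5 | 37% | – | 31% |
| 0.7 | 50% | 43% to 44% | 48% to 49% |
| 0.85 | 76% | 69% | 79% |

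The loss from screening was about 4 to 7 points over the settings tried. The gated test is behind the fixed model at r = 0.5, about level at 0.7 and ahead at 0.85.

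**The case against.** The strongest reply is that the article does label a primary analysis, with its endpoint, scale and core covariates. The gated tests sit in a general paragraph with descriptive summaries and contingency tables, and are probably the univariate analyses mentioned later. The statistician is blinded during the study, a separate analysis plan may set the covariate rule, and all the inflation above assumes picking among results, which the text does not prescribe.

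Much of this stands, and it rules out several stronger readings that a reader might infer:

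- *That no primary analysis is fixed, or that the gate replaces the regression.* The regression is expressly called primary. The gate is a competing comparison of unstated rank.
- *That screening or gating by itself inflates type I error.* Each rule used alone stays near 5%.
- *That the outcome is ambiguous in a way that matters.* The Outcomes section says "The primary outcome of this trial is 6MWD measured at 16 weeks", whereas the abstract and the analysis section speak of change. In the baseline-adjusted model the two give the same result (step 3). A larger inflation would need an unadjusted test of the week-16 value as a further option, and the article never names that analysis.
- *That the gated test on change is clearly weaker.* The ordering depends on r (step 4).

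What the reply does not remove is the covariate sentence. It states a data-driven choice of the final model, and blinding until last follow-up does not mean the choice is made before unblinding.

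**Conclusion.** The point holds in limited form. The core of the primary model is specified; its final covariates are not, and a second test of the same outcome has no stated rank. If the freedom is used, the false-positive rate is roughly 8% to 10% instead of 5%. If one rule is followed mechanically, it is about 5%, and the cost of screening uninformative covariates is about 4 to 7 points of power.

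These sizes rest on 27 completers, 5 to 10 candidates, entry at p < 0.10 or 0.20, at most four additions and, for power, the assumed r. They show what the wording permits, not what the team will do. The analysis is to include all randomized subjects, so the actual number may be nearer 30. The wording should be changed before unblinding.

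**What to change.** 1. Strike univariate screening for the primary model.
2. Before unblinding, fix that model as change in 6MWD on treatment, baseline 6MWD, age, sex and center. Center is the randomization stratum and is missing from the named model.
3. Label covariate-extended models, and the unadjusted t, transformed and Wilcoxon comparisons, as supportive.
4. Check the residuals of the fixed model instead of gating on the distribution of the raw outcome. A permutation test within center could be named as a sensitivity analysis, but is optional.

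The cost is analysis wording only. The team gives up the option of adding a strong unforeseen predictor to the primary model, and center uses one degree of freedom.

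### The two four-term logistic models for the MID responder analysis will overstate a true treatment odds ratio in about 27 patients, and the clinical-relevance role of the responder proportions should be worded as supportive only

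*Protocol article*

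**What the plan says.** The Data analysis plan of the protocol article makes the adjusted linear model of change in 6MWD the primary analysis. It then compares the proportions reaching the MID at two cut-offs, 33 m (from PAH) and 24 m (from SSc-PAH). The adjusted form of that comparison is fitted "Using separate multivariable logistic regression models adjusting for baseline walk distance, age, and sex", one model per cut-off. No penalised or exact estimation is mentioned, so ordinary maximum likelihood is assumed here.

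The same section says: "Hypothesis testing will use two-sided α = 0.05 without correction for multiplicity". It adds an optional further step: "We can then perform responder analyses to determine characteristics of SSc-MEP patients likely to achieve either MID".

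The Sample size section plans on 27 completers of 30 enrolled. It gives the responder proportions a particular role: "if differences in 6MWD observed in the study do not reach the predefined detectable alternative", they may be used to show whether the effect on 6MWD is clinically relevant. The detectable alternative is 45 m. The section also says that the MID in SSc-MEP is not known.

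**The concern.** There are two separate problems.

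- **Estimation.** Logistic regression by maximum likelihood is biased away from an odds ratio of 1 when the rarer outcome class is small for the number of terms. The Data analysis plan warns of overfitting in its text on the linear model, but carries the same covariates to a binary outcome that holds less information. The results are meant to inform a phase 3 study, so an inflated odds ratio could mislead its planning.
- **Interpretation.** The responder comparison is called on when the mean difference disappoints. It has two cut-offs and no multiplicity control. Unless it is labelled as supportive, a chance responder result could be read as clinical benefit after a non-significant primary result.

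**Working it through.** **1. The plan's own figures.** The article gives no power or sample size for the responder models. Its dropout step reproduces: 27/0.9 = 30. For the primary it claims "> 80% power to detect this difference at significance level of 0.05 with 27 subjects", from 45 m and an SD of 75 m. A two-arm test of 14 against 13 with these inputs has power of 0.32 (t) to 0.34 (normal). Only a one-sample or paired test reaches the claim (0.851). That is a separate point. It matters here because it makes a disappointing mean difference more likely.

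**2. Patients per model term.** The terms are treatment, baseline 6MWD, age and sex, four in all.
- Ceiling with 27 patients: 13/4 = 3.25 per term. With all 30 randomized: 15/4 = 3.75. Neither needs an assumption.
- Example (assumed: normal change, placebo mean 0, SD of change 75 m, cut-off 33 m). Placebo responders: 1 − Φ(33/75) = 0.330. Sildenafil responders with a 45 m effect: 1 − Φ((33 − 45)/75) = 0.564. Expected responders: 13 × 0.330 + 14 × 0.564 = 12.2, or about 3.0 per term. With no effect: 27 × 0.330 = 8.9, or 2.2 per term.

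**3. Bias in the treatment odds ratio.** Simulated trials of 27 patients, true effect 45 m, cut-off 33 m. The reference is the same four-term model in a very large sample, so the comparison is like with like.

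| Assumed correlation | Mean log OR, maximum likelihood | Large-sample log OR |
|---|---|---|
| 0.7 | 1.82 (median about 1.65) | 1.42 |
| 0.5 | 1.46 | 1.16 |

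At correlation 0.7 this is exp(1.82) = 6.2 against exp(1.42) = 4.1, a factor of exp(0.40) = 1.49. By the median the factor is exp(1.65 − 1.42) = 1.26. At correlation 0.5 it is exp(0.30) = 1.35. With no true effect the mean log odds ratio is about zero. Firth penalisation at correlation 0.7 gave 1.41, close to the reference of 1.42.

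**4. Precision.** In a separate simulation (SD of change 75 m, effect 45 m, 30% or 50% men assumed), the upper limit of the 95% CI for the treatment odds ratio was typically 48 to 50 times the lower limit.

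**5. Models that fail.** The treatment coefficient was non-estimable in about 2–4% of simulated trials. At least one coefficient failed in about 22–38% with 15% men and 5–12% with 30% men. Both sex mixes are assumptions, because the article gives none. Most failures are in the sex term.

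**6. Extra chances of a positive result.** With no effect, the chance that the primary or either responder model has p < 0.05, in either direction, was 6.5–8.2% with Wald tests and 9.4–12.5% with likelihood-ratio tests. Taking a Fisher test as well gave up to 13.2%. The primary alone has 5%. Three independent tests would give 1 − 0.95³ = 14.3%. The actual figure is lower because all three use the same walk distances.

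**7. How the trigger relates to significance.** The trigger is an observed difference below 45 m. With an SD of 75 m, an unadjusted test needs about 2.06 × 75 × √(1/13 + 1/14) = 59.5 m for significance, so a difference below 45 m would not be significant. With adjustment at an assumed correlation of 0.7 the SD falls to 75 × √(1 − 0.49) = 53.6 m and the threshold to about 43 m, close to the trigger. If the true effect is exactly 45 m, the observed difference falls below it about half the time.

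**The case against.** The strongest reply is that this is a supportive analysis in a phase 2 trial. The primary is fixed as the adjusted linear model, and the article says openly that it makes no multiplicity correction. The wording on clinical relevance is soft. The unadjusted proportions are already to be compared, and the estimation method may be set in an SAP that is not shown. All of this stands and keeps the point minor. It does not remove it, because the article itself fixes the four terms, the two cut-offs and the clinical-relevance role.

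A reader might infer four stronger things that the documents do not support.

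- **That the treatment odds ratio will often be non-estimable.** The high failure rates belong mainly to the sex term and to an assumed low share of men. The treatment term fails in only about 2–4% of trials.
- **That a responder result may formally replace the primary.** The trigger is an observed difference below 45 m, not a non-significant p-value, and no text permits substitution. The near-coincidence in step 7 explains why a clarifying sentence is useful. It does not show that a rescue is planned.
- **That the search for responder characteristics rests on only the treated half.** The text does not restrict it to the sildenafil arm, and it is worded as optional.
- **That age and sex must be dropped.** They match the primary model. Removing them is a trade-off, not a correction.

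**Conclusion.** The concern holds in a limited form, and its severity is minor. That there are at most 3.25 patients per term (3.75 with all 30) follows from the article's own numbers. The size of the bias rests on assumptions: a normal distribution, a baseline-to-follow-up correlation of 0.5 to 0.7, an effect of 45 m and the 33 m cut-off. Under these the odds ratio is overstated by a factor of about 1.35 to 1.5 on the mean log scale, and by less at the median. There is bias only if the treatment works, so the bias does not create an effect from nothing. The rise in error from 5% to about 7–13% is moderate. It depends on the test used, and it arises only if a responder result is counted as a success.

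**What to change.** 1. In the Data analysis plan, fit both responder models by Firth-penalised logistic regression with profile-likelihood confidence intervals. Age and sex can stay. Beside each model, report the unadjusted risk difference at that MID with a score or exact 95% CI.
2. In the Sample size section, state that the responder proportions are supportive only and cannot replace or reinterpret a non-significant primary result.

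The cost is slightly more analysis work and, usually, an odds ratio nearer to 1. No change to design, sample size or data collection is needed. If the SAP already specifies penalised estimation, only the reporting of the risk difference and the second change remain.
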